## PROTOCOL SUMMARY

**Short Title:** **STOP (STD Testing in Outpatient Practices) STDs STUDY**

**Principal Investigator:** [name] , M.C., C.M.

**Study Population:** Primary care practices and obstetrics and gynecology practices affiliated with the University of Pittsburgh Medical Center (UPMC) in Western Pennsylvania providing care to women 18-24 years old.

**Study Design:** A randomized pragmatic cluster trial of an alert in the electronic health record directed at medical assistants during the rooming in of patients to offer chlamydia and gonorrhea screening in primary care and obstetrics/gynecology (OBGYN) practices.

Primary care and OBGYN practices will separately be randomized to the intervention (electronic alert) and control groups (usual care). Medical assistants in practices randomized to the Intervention will receive a real-time alert reminder in the electronic medical record (EMR) to offer chlamydia and gonorrhea screening to patients likely eligible for screening during rooming in for office visits. In practices randomized to the control arm, no alert will be provided. The main outcome of the study is chlamydia test orders, which will be compared between the intervention (alert) and control arms, separately for primary care practices and for obstetrics/gynecology practices.

## 1. Background and Rationale

Routine screening of sexually active young women for *Chlamydia trachomatis* and *Neisseria gonorrhoeae* is recommended in order to prevent the development of pelvic inflammatory disease and to reduce transmission of these sexually transmitted organisms. Young women are disproportionately burdened by chlamydia and gonorrhea, and adolescent females have had the highest prevalence of infection. Based on estimates from national surveys conducted from 1999–2008, chlamydia prevalence among sexually active females aged 14–19 years was 6.8% overall and 16.2% among non-Hispanic black women. Analysis of LabCorp chlamydia testing data from 2008–2010 found that chlamydia positivity ranged from 6.9%–10.7% among women aged 15–21 years with chlamydial symptoms, and 6.1%–9.6% among asymptomatic women.

Sexually transmitted diseases are associated with adverse reproductive health outcomes and increased HIV transmission. Chlamydial and gonococcal infections in women are often asymptomatic and when untreated can result in complications such as pelvic inflammatory disease (PID) with long term reproductive sequelae of infertility, ectopic pregnancy, and chronic pelvic pain. As these infections are commonly asymptomatic in women, screening for these infections in at-risk individuals is important to enable earlier detection and treatment and the protection of reproductive health of women. Two randomized controlled studies found that chlamydia screening and treatment decreased the incidence of PID.

As most women infected with chlamydia and gonorrhea are asymptomatic, screening programs have been key strategic components of prevention efforts. Despite national screening recommendations, screening rates among young women have been suboptimal. Only 11% of 0.5 million sexually active women aged 15 years reported being tested for chlamydia in the prior year. Among women aged 15–21 years, chlamydia testing occurred very infrequently at visits to pediatricians (< 1%), and in only 28% of visits to a physician where a Pap test was performed. Several barriers to chlamydia screening have been identified. Taking a sexual history, particularly from younger patients is especially challenging. Providers may not recognize the need to screen at-risk patients. Many competing demands and priorities in an often brief clinical encounter can also be a barrier to STD screening, especially given the sensitive discussion about sexual behaviors that is necessary to identify those who should undergo screening. As such, novel strategies are urgently needed in order to overcome these barriers and increase screening rates for chlamydia and gonorrhea.

Interventions to increase chlamydia and gonorrhea screening directed to the providers have only been moderately effective. Clinical decision support systems, including clinician-facing electronic alerts that generate patient-specific recommendations, are widely used to promote best practices. However, a systematic review of point-of-care electronic alerts directed at physicians yielded only a modest effect, with a median care improvement of only 4.2%. The sheer number of alerts can desensitize a busy physician and cause alert fatigue, leading to ignoring or dismissing the alerts. Medical assistants generally do not receive alerts about clinical care and therefore might be less likely to face alert fatigue. Medical assistants might be more likely to interact with alerts

than other clinicians as they work under the direction of medical leadership of their practices. Further, an intervention directed at medical assistants during rooming in of patients could avoid burdening clinicians with additional tasks.

## **2. Study Objectives**

The hypothesis of this study is that proportion of women ordered chlamydia screening will be higher in practices randomized to an electronic alert directed at medical assistants during rooming in of patients for their office visit than in practices without the electronic alert. Our primary objective is to compare the test order rates for *C. trachomatis* between practices randomized to the electronic alert compared to practices operating under routine care, separately for primary care practices and OBGYN practices. The secondary outcome will be to determine the test order rate in visits for reproductive care compared to visits for other medical reasons.

## **3. Trial Design: Randomized pragmatic cluster trial**

## **4. Study Population**

Primary care practices will be recruited from two large primary care groups in the UPMC Health System. These groups contain family medicine and internal medicine practices. Obstetrics and gynecology practices affiliated with the Department of Obstetrics, Gynecology and Reproductive Sciences at UPMC will be recruited. Practices must be utilizing EPIC (Epic Systems Corporation, Verona, Wisconsin) as their EMR. Medical leaders at each site will be approached for their interest in participating in this randomized trial. Practices whose leaders agree to participate will be potentially eligible for participation.

## **5. Study Procedures**

### **5.1 Electronic Alert**

An automated alert will be developed with the assistance of the UPMC informatics group. The electronic alert will be generated at the time of the office visit for practices in the intervention arm if the following criteria are met (all must be present):

1. Female patients (defined as the designated legal sex previously populated in the demographic section of the electronic health record)
2. Age 18-24
3. Non pregnant (defined as the absence of an active Pregnancy Episode in the EMR)
4. No order for a chlamydia test in the EMR in the preceding 365 days

The alert contains brief information about the importance of chlamydia and gonorrhea screening to women's health. The alert will be directed at the medical assistant during the beginning of the patient's visit, typically during the rooming process as patients are being prepared for the visit with the provider. The alert will inform the medical staff that chlamydia and gonorrhea screening is recommended for sexually active women age 24 and younger and will provide an option to place an order. A hyperlink button linked to the order entry will be in the alert, with chlamydia and gonorrhea orders on display for ordering by the MA for later signature by the clinicians.

Wording of the Alert: The electronic alert will contain the following wording:

"Routine annual chlamydia and gonorrhea screening is recommended for all sexually active women age 24 and younger. Please use SmartSet to order screening by urine sample or self-collected vaginal swab if appropriate, or indicate the reason for not placing orders today"

TABS:            OPEN SMARTSET            DO NOT OPEN SMARTSET

Acknowledge Reason (tabs):

NOT SEXUALL ACTIVE            PATIENT DECLINED            SCREENED IN LAST YEAR

## 5.2 Study Arms

Intervention Arm (Electronic Alert) of Office Practices: Sexually active women 18-24 years old seeking care at practices randomized to the intervention group will be offered screening by the office staff (medical assistant) at the time of the visit. An automated alert generated in the EMR will direct the staff member to offer chlamydia and gonorrhea screening to eligible women.

Control Arm of Office Practices: Screening for chlamydia and gonorrhea will be at the discretion of the physicians or advanced-care providers per their usual care. The electronic alert will not be active in these practices.

## 5.3 Site Selection and Randomization

Practices will be categorized by type of practice/specialty [primary care and OBGYN], location (metropolitan /urban vs. rural), and proportion of patients categorized in the EMR as African American. Primary care practices must have provided care to at least

200 females aged 16-24 in the previous year to be eligible for participation. Practices will then be matched and randomized to the intervention or control groups. Details on randomization are included in the Statistical Analysis Plan.

#### **5.4 Procedures in the Intervention Arm**

Staff at the office practices randomized to the intervention group will undergo a brief 30 minute educational session by the principal investigator that will include a review of the screening guidelines and the importance of chlamydia and gonorrhea screening for women's reproductive health. During that session, the staff at each practice, typically medical assistants will be advised to offer screening without coercion. Staff will have the option of ordering a test by urine sample or self-collected vaginal swabs according to practice and patient preference. Staff will be informed that screening is typically performed at no cost to the patient if the patient has medical insurance. The EMR alert will include a link that will direct the staff to the order entry section of the record, with options for chlamydia and gonorrhea tests embedded into the order screen. The order will be placed and held (also known as "pending") for later signature by the physician or advanced practice provider.

Staff leaders (e.g. office managers) at the Intervention sites will be contacted by the research assistant by telephone at three month intervals. The sole purpose of these calls is to verify that the staff are receiving the alerts, thereby confirming that the EMR alerts are functioning properly. Office practices will have the opportunity to raise any safety concerns at that time. No additional educational training or information will be shared by the research staff member during these contacts.

#### **5.5 Procedures in the Control Arm**

Office practices randomized to the control arm (usual care) will not have the alert activated in their EMR. The staff will not receive an educational session, nor will they be contacted during the study period.

### **6. Microbiologic Testing**

Urine or self-collected vaginal swab samples (at the discretion of the office practice/staff and the patient) will be obtained for *C. trachomatis* and *N. gonorrhoeae* testing. Samples will be sent per office routine to their preferred microbiology laboratories, often those affiliated with UPMC (UPMC labs and Quest Laboratories). Testing will typically be performed using the APTIMA platforms per the routine of the labs in Western Pennsylvania. Costs of these tests would be charged to the patient's insurance provider, and insured patients will not have any cost for the test as chlamydia and gonorrhea screening are recommended preventive care and therefore are covered services. The results of screening will be reported back into the EMR for review by the clinical team per usual routine if the laboratory interfaces electronically with UPMC's EMR. Infections will be treated per office/provider routine.

## **7. Data Collection and Management**

The research informatics team at UPMC (CARE, see below) will capture pertinent clinical data in EMR for women attending in both the intervention and control practices. They will provide demographic and clinical information for data analyses that will include age, race, reason for visit, clinical services performed, chlamydia and gonorrhea test orders, and test results (if test results are available). All data will be de-identified prior to transfer to the investigators and to the CDC for data analyses.

The Center for Assistance in Research using eRecord (CARE) provides facilitated managed, compliant and secure access to the UPMC Electronic Health Record for researchers. CARE utilizes the EMRs and databases in use by UPMC. EMRs are currently deployed in both inpatient and outpatient clinics throughout the health system and provide a wealth of information for investigators. EpicCare is the EMR product in use in ambulatory clinics and outpatient offices affiliated with UPMC. The data contained in the EMRs are maintained behind a secure firewall on servers within the UPMC data center.

## **8. Sample Size Calculation**

Assuming that the screening rate in the usual care group is 30% and in the opt-out group it will be 35%, a study recruiting 1882 patients in the usual care group and 1882 patients in the opt-out group will result in 90% power to detect a significant difference in the proportion of women screened for chlamydia at a two sided .05 significance level. As such we propose to recruit at least 2000 patients in the opt-out group and 2000 patients in the usual care group.

If the baseline screening is closer to the 2011-2012 average commercial (non-Medicaid) screening rate of sexually active women (40% in 16-20 year olds and 47% in 21-24 year olds) we would need to enroll 898 women ages 16-20 and 228 women ages 21-24 in order to demonstrate a 20% increase in screening at 90% power. The proposed study would provide enough power to examine both of these age groups.

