### **Statistical Methods**

In this study, we will employ the following statistical methods to analyze the impact of a real-time alert system on chlamydia screening orders:

- **Baseline Characteristics:** Baseline characteristics will be summarized by study arm within each cohort (primary care and obstetrics/gynecology). Between-arm differences may be evaluated using 2-sided hypothesis tests ( $\alpha = 0.05$ ); however, P values will not be presented in Table 1. As a supplementary, sample size-independent measure,

standardized mean differences (SMDs) may also be calculated to aid interpretation of the magnitude of baseline differences and, if used, will be summarized briefly in the text.

- **Constrained Difference-in-Differences Mixed Effects Logistic Regression (Primary Approach):** We will estimate the intervention effect using a constrained difference-in-differences mixed-effects logistic regression model with a logit link. The model will include fixed effects for time period and the time-by-intervention interaction to compare pre-to-post changes between intervention and control practices. Random intercepts for practice (cluster) and patient will be included to account for within-cluster correlation and repeated encounters within patients. Models will be fit separately for primary care and obstetrics/gynecology practices. We will also report the intraclass correlation coefficient (ICC) to quantify the within-cluster correlation in the outcome, which is relevant for interpreting clustering and the precision of cluster-randomized estimates.
- **Small-Sample Inference for Cluster Randomized Designs:** Because the number of randomized clusters is fewer than 50, 95% confidence intervals and P values will be constructed using a t distribution with degrees of freedom (df) equal to  $K - p$ , where  $K$  is the number of clusters, and  $p$  is the number of cluster-level covariates included in the model.

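### Section 8's 90% power is calculated for independently sampled patients and is unsupported for a trial that randomises practices

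*Combined protocol and SAP*

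**What the plan says.** Section 8 of the protocol begins "Assuming that the screening rate in the usual care group is 30" percent and supposes that "in the opt-out group it will be 35" percent (opt-out is that section's label for the alert arm). It concludes that "a study recruiting 1882 patients in the usual care group and 1882 patients in the opt-out group will result in 90% power" to find a difference "at a two sided .05 significance level". It then proposes at least 2000 patients per arm. It does not say whether that number applies to each cohort or to both together.

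The heading of Section 3 calls the study a "Randomized pragmatic cluster trial". The protocol summary and the SAP's Randomization section confirm that practices are the randomised unit, 1:1, separately for primary care and for obstetrics/gynecology.

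The SAP's Statistical Methods section plans for clustering: "Random intercepts for practice (cluster) and patient will be included to account for within-cluster correlation". It also uses a t reference distribution because there are fewer than 50 clusters, and it promises to report an ICC as a result. The SAP's Significance Levels section tests each cohort's primary comparison at 0.025.

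The only practice-size figure is the entry rule for primary care in Section 5.3, "200 females aged 16-24 in the previous year to be eligible for participation". Neither document gives a planning ICC, a design effect, the number of practices per arm or a cluster-adjusted sample size.

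**The concern.** When practices are randomised, women at the same practice share clinicians and ordering habits, so each additional woman there adds less information than an independent one. A formula for independent patients then overstates power, increasingly so with more women per practice and a higher ICC. The analysis plan treats this correlation as material, while the sample size gives no sign of it.

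Section 8 holds the only power justification for the primary outcome. A reader who trusts the 90% would take a non-significant result as fairly strong evidence against a 5-point gain, when the true chance of detecting that gain could be much lower.

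**Working it through.** **Inputs from the documents.** p1 = 0.30, p2 = 0.35, two-sided 0.05, 90% power, 1882 and then 2000 per arm (Section 8); fewer than 50 clusters (SAP, Statistical Methods); 0.025 per cohort (SAP, Significance Levels).

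**Assumptions.** ICC of 0.01 or 0.02. Either 24 practices per arm (48 in all, the most that fewer than 50 allows with an even split, all in one cohort) or 10 per arm (which makes 2000 women equal to 200 per practice). The documents give neither the ICC nor the number per arm.

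**Step 1: reproduce 1882.** With p̄ = 0.325 and d = 0.05:

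n = [1.960·√(2·0.325·0.675) + 1.2816·√(0.30·0.70 + 0.35·0.65)]² / 0.05² = (1.2982 + 0.8477)² / 0.0025 = 1841.97.

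Continuity correction: (n/4)·[1 + √(1 + 4/(n·d))]² = 1881.76, which rounds up to 1882. The match is exact, and the formula has a design effect of 1.

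**Step 2: margin at 2000 per arm.** Power is Φ{[d√n − z·√(2p̄(1−p̄))] / √(p1(1−p1) + p2(1−p2))}. At n = 2000 this is 92% at alpha 0.05. At alpha 0.025 (z = 2.241) it is 87%. Both ignore clustering.

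**Step 3: ICC at which 90% is lost.** The uncorrected requirement is 1842, so the tolerable design effect is 2000/1842 = 1.086. Setting 1 + (m−1)·ICC = 1.086, where m is women per practice:
- 24 practices per arm, m = 83.3: ICC = 0.086/82.3, about 0.001.
- 10 practices per arm, m = 200: ICC = 0.086/199, about 0.0004.

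**Step 4: power at 2000 per arm, alpha 0.05.** DE = 1 + (m−1)·ICC, and effective n = 2000/DE. To credit the SAP's baseline period, DE is multiplied by (1 − r²), where r = m·ICC·0.8/DE. This assumes equal-sized pre and post samples and a between-period practice correlation of 0.8.

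| Practices per arm | ICC | DE | Effective n | Power | DE with baseline | Power with baseline |
|---|---|---|---|---|---|---|
| 24 | 0.01 | 1.82 | 1097 | 71% | 1.58 | 77% |
| 24 | 0.02 | 2.65 | 756 | 55% | 1.97 | 67% |
| 10 | 0.01 | 2.99 | 669 | 50% | 2.13 | 64% |
| 10 | 0.02 | 4.98 | 402 | 33% | 2.92 | 51% |

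**Step 5: the SAP's own alpha and reference distribution.** At alpha 0.025 and ICC 0.01, the power figures without baseline fall from 71% and 50% to 60% and 39%. A t reference with K − 2 degrees of freedom (46 and 18, taking K as 48 and 20) lowers them further, to 58% and 34%.

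**The case against.** The strongest reply is that 2000 is a floor and data come from electronic record capture of women attending the practices (Section 7), so actual numbers may be much larger. This stands. With 24 practices per arm and 200 women in each (4800 per arm), ICC 0.01 and the same baseline credit, DE is 2.13, effective n is 4800/2.13, about 2250, and power is 95% at alpha 0.05. A reader might therefore infer from the missing design effect that the trial cannot deliver 90% power. The documents do not support that inference, because they fix neither the number of practices nor the number of women. The example is a best case, though, since it places nearly all the permitted practices in one cohort. It also needs more practices: with 10 per arm and unlimited women, effective n cannot exceed 10/ICC = 1000 at ICC 0.01, so power without baseline is capped at 67%.

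A reader might also suppose that the obstetrics/gynecology cohort is the smaller one and so the worse affected. No section gives the size of either cohort.

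Nor is 200 women per practice a planned cluster size. The Section 5.3 threshold counts all females aged 16–24 seen in a year, whereas the alert covers non-pregnant women aged 18–24 with no chlamydia order in the preceding 365 days. It is also a minimum, so some practices will be larger.

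Finally, the primary analysis models practice, uses a t reference and reports confidence intervals. Omitting clustering from Section 8 therefore does not bias the estimate or inflate type I error, and the intervals limit misreading of a null result. That confines the defect to the power claim without removing it.

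**Conclusion.** The point holds as a defect in the stated justification. That 1882 is an independent-patient number follows from the documents alone. That 90% fails at 2000 per arm unless the ICC is about 0.001 or less also depends on the SAP's limit of fewer than 50 clusters. The baseline period recovers part of the loss in the scenarios examined but does not restore 90% at that sample size, and Section 8 does not invoke it.

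The size of the loss cannot be fixed. The range from 33% to 77% at alpha 0.05 is a sensitivity range over assumed ICCs, practice counts and baseline correlation, and is not an estimate of this trial's power. The conclusion is that the 90% is unsupported; whether the realised trial is underpowered is unknown. The statement should be corrected because it is the only power claim for the primary outcome and restating it is cheap.

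**What to change.** Replace the 90% statement in Section 8 with power for 30% versus 35%, or the detectable difference, given separately for the primary care and the obstetrics/gynecology cohort. For each cohort:
- use two-sided alpha 0.025, as the SAP's Significance Levels section requires;
- state the actual number of practices per arm and the expected number of eligible women per practice;
- apply a design effect of 1 + (m−1)·ICC over a stated ICC range, or with an ICC estimated from pre-period record data;
- if the baseline period is credited, state the assumed pre and post sample sizes and between-period correlation;
- use the t reference distribution from the SAP's Statistical Methods section.

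The cost is a rewritten paragraph and a probably less favourable power figure. It needs no added enrolment or data and no change to the analysis.

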## **Significance Levels**

The familywise significance level will be set at  $\alpha = 0.05$  (2-sided). Because the primary endpoint will be evaluated in 2 parallel cohorts (primary care and obstetrics/gynecology practices), we will apply a Bonferroni correction, using  $\alpha = 0.025$  per cohort-specific primary comparison. For secondary outcomes, hypothesis tests will be interpreted using a 2-sided significance threshold of  $\alpha = 0.05$  unless otherwise specified.

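### Sample size is powered for one comparison at two-sided 0.05, but the primary analysis is two separate cohort tests at 0.025 each, so the claimed 90% power is not met

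*Combined protocol and SAP*

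**What the plan says.** Protocol Section 8 (Sample Size Calculation) takes a usual-care screening rate of 30% and an intervention rate of 35%. It states that 1882 in usual care and "1882 patients in the opt-out group will result in 90% power to detect a significant difference", with the test made "at a two sided .05 significance level". It then rounds up: "we propose to recruit at least 2000 patients in the opt-out group and 2000 patients in the usual care group". The section's second paragraph gives further scenarios by age group, none by practice type.

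The primary analysis is set out differently elsewhere:

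- The Protocol Summary compares chlamydia test orders between arms "separately for primary care practices and for obstetrics/gynecology practices", and Section 2 repeats this in the primary objective.
- The SAP (Randomization) randomizes the two practice types separately, 1:1.
- The SAP (Statistical Methods) fits a separate model for each practice type.
- The SAP (Significance Levels) says: "Because the primary endpoint will be evaluated in 2 parallel cohorts (primary care and obstetrics/gynecology practices), we will apply a Bonferroni correction". The resulting level is 0.025 for each cohort's primary comparison.

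**The concern.** Section 8 and the SAP disagree on two inputs to the power calculation. The first is alpha: 0.05 in the sample size, 0.025 in the test. The second is the unit: one undivided pair of totals in the sample size, two separately randomized and analysed cohorts in the test. No pooled primary test at 0.05 is planned, so the 90% describes a test the trial will not perform.

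This matters most if one cohort gives a null result. A reader would use the stated 90% to judge whether the null is evidence against a 5-point effect. If the true figure is in the eighties, that reading is somewhat optimistic. If it is in the fifties, a null result says little.

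**Working it through.** **Inputs.** From Section 8: p1 = 0.30, p2 = 0.35, d = 0.05, 90% power, two-sided alpha 0.05, 1882 per arm, planned minimum 2000 per arm. From the SAP: two-sided alpha 0.025 per cohort, two cohorts, 1:1 allocation. The arm that Section 8 calls opt-out is taken to be the alert arm. Patients are treated as independent, as Section 8 implicitly does.

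**Formula.** With p̄ = 0.325:

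- S0 = √(2 × 0.325 × 0.675) = 0.66238
- S1 = √(0.30 × 0.70 + 0.35 × 0.65) = 0.66144
- n = (z(1−α/2) × S0 + z(0.90) × S1)² / d²
- with continuity correction, n′ = (n/4) × (1 + √(1 + 4/(n × d)))²

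**Step 1. Reproduce the plan's figure (alpha 0.05).**

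- n = (1.9600 × 0.66238 + 1.2816 × 0.66144)² / 0.0025 = 1842.0
- n′ = 1881.8, which rounds up to 1882

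The match is exact with the continuity correction. Section 8 names no method, so the correction is inferred from the match; results are given both ways below.

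**Step 2. Same formula at the SAP's alpha (0.025).**

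- n = (2.2414 × 0.66238 + 1.2816 × 0.66144)² / 0.0025 = 2175.9, so 2176 per arm per cohort
- n′ = 2215.7, so 2216 per arm per cohort
- Like for like this is 18% more: 2176/1842 = 1.18 and 2216/1882 = 1.18
- For two cohorts of two arms: 4 × 2176 = 8704, or 4 × 2216 = 8864 with correction, against 4000 if the stated numbers are the trial total

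**Step 3. Power at alpha 0.025 for the stated numbers.** Power = Φ((d√n − z(1−α/2) × S0) / S1). For the corrected version, d is replaced by d − 1/n.

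| Women per arm in a cohort | Power | With continuity correction |
|---|---|---|
| 2000 (2000 per arm in each cohort) | 87.2% | 86.5% |
| 1882 | 85.0% | 84.1% |
| 1000 (2000 per arm shared equally) | 55.8% | 53.9% |

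Worked case, n = 2000: (0.05 × 44.721 − 2.2414 × 0.66238) / 0.66144 = 1.136, and Φ(1.136) = 0.872. At alpha 0.05 the same 2000 per arm gives 92.2% (91.7% corrected), which is the margin Section 8 appears to rely on.

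**Step 4. Range for an uneven split.** The documents give no split of 2000 per arm between cohorts. Uncorrected power at alpha 0.025 is 23% for a cohort with 400 per arm, 35% with 600, 72% with 1400 and 78% with 1600.

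**Step 5. Direction of clustering.** Section 8 gives no ICC, cluster size or design effect. As an illustration only, with 2000 per arm in each cohort at alpha 0.025, an assumed design effect of 1.5 gives about 70% power and one of 2 gives about 56% (uncorrected).

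**The case against.** The strongest case on the other side has five parts.

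- **1882 is correct for its own inputs.** It is. The fault is that those inputs are not the primary analysis's inputs.
- **The 2000 is a minimum.** Data come from the electronic record for women attending the practices, with no stated cap, so the numbers may well be larger. Section 5.3 requires at least 200 females aged 16-24 in the previous year at each primary care practice, and 11 such practices per arm would give 11 × 200 = 2200. This stands as a reason not to claim that the trial itself will be underpowered. But the number of practices is not given, the 200 covers a wider age range than the alert's 18-24 and women who may not meet its other criteria, and the rule does not apply to obstetrics/gynecology practices. The plan does not base its 90% on any such surplus.
- **The 56% figure needs two assumptions:** that 2000 per arm is the whole trial, and that it splits equally. That is right, and it should be read only as that scenario. On the favourable reading the loss is about 3 points.
- **The 30% baseline may not hold in both cohorts.** For the same 5-point difference with 2000 per arm at 0.025, uncorrected power is 94% from a 20% baseline, 90% from 25%, 87% from 30% and 83% from 40%. A lower baseline would close the gap, but the plan's claim is made at 30%.
- **The two-proportion test is not the primary model,** which is a constrained difference-in-differences mixed logistic regression with t-based inference. True: the figures here check the stated calculation and are not the trial's actual power. Baseline-period data may recover some precision, but the plan claims no such gain, and clustering and the t reference work the other way.

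The mismatch also biases no estimate, and the Bonferroni rule protects the type I error. The point concerns the stated power only.

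**Conclusion.** The concern holds. On the plan's own rates and with independent patients, the stated minimum does not give 90% power for either primary test as the SAP defines it. The size depends on a question the documents leave open. If 2000 per arm applies to each cohort, power is 87% (86% corrected), a modest shortfall. If it is the trial total, as the single pair of totals suggests, and the cohorts are equal in size, each test has 56% (54% corrected), close to a coin flip. An uneven split would leave the smaller cohort lower still.

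These results rest on 30% against 35% in both cohorts, equal arms, enrolment at the stated minimum and no clustering. The problem is separate from clustering: adding a design effect alone would leave both the alpha and the cohort split wrong.

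**What to change.** In Section 8:

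1. Say whether 2000 per arm is per cohort or for the whole trial, and give the target or expected number for primary care and for obstetrics/gynecology separately.
2. Recompute power for each cohort at two-sided 0.025, with that cohort's assumed usual-care rate, and replace the statement of 90% power at 0.05 with the results.
3. Make the clustering correction in the same revision, stating the assumed ICC, number of practices and cluster size, so that alpha, unit and design effect all match the primary analysis.

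The cost is one paragraph and a less favourable power figure. The design, the primary model and the alpha allocation stay as they are, and no added enrolment is required. The SAP describes randomization in the past tense, so the restatement may come too late to shape the design, but it is still needed to interpret a null result in either cohort.
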